**Clinical Trial Protocol**

**Version 3.0**

**Research Protocol Synopsis**

| **Name of cell product** | Umbilical cord-derived mesenchymal stem cells |
| --- | --- |
| **Trial title** | A clinical trial of umbilical cord-derived mesenchymal stem cells for the treatment of refractory immune thrombocytopenia |
| **Trial Objectives** | Primary objective: To observe the incidence of adverse events in patients after umbilical cord-derived mesenchymal stem cell (UC-MSC) infusion, and to preliminarily evaluate the safety of clinical infusion of UC-MSCs.  Secondary objectives: To preliminarily evaluate the effectiveness of UC-MSCs in the clinical treatment of refractory ITP patients through this clinical study. |
| **Trial design** | A single-centre, open-label, single-arm study |
| **Main inclusion criteria** | 1) 18-60 years of age, regardless of gender;  2) Confirmed diagnosis of ITP for at least 6 months with an insufficient response to first-line treatment drugs (IVIG, corticosteroids), thrombopoietin drugs and rituximab in second-line, or failed to response or relapsed after splenectomy;  3) Subjects who received splenectomy or rituximab must have finished the therapy more than 3 months prior to enrollment;  4) Platelet counts < 30×10^9^/L with bleeding;  5) Expected survival time for at least 6 months;  6) The function of liver and kidney is less than 1.5 times the upper limit of normal value, and the physical examination is qualified;  7) ECOG physical status score ≤ 2;  8) Cardiac function: grade 2 or below according to the New York Society for Cardiac function;  9) Voluntarily sign the informed consent. |
| **Timepoint and**  **index of**  **efficacy evaluation** | Detect and record the platelet counts at 1, 2, 3, 4, 5, 6, 7, 8, 9, 10, 11, 12, 16, 20, and 24 weeks after 4 times infusion, evaluate the changes in peripheral blood platelet counts. |
| **Safety evaluation index** | Vital signs of the subjects and adverse reactions related to UC-MSCs infusion such as fever, embolism, vomiting, diarrhea, rash, and hepatitis B, hepatitis C, and other virus infections are observed immediately after the first infusion to the 4th month (16w) visit period. |

、

| **Number of subjects** | At least 15 cases |
| --- | --- |
| **Cell product specification** | Umbilical cord-derived mesenchymal stem cells, mainly composed of human umbilical cord-derived mesenchymal stem cells in vitro, 5mL/bag, containing 2.0×10^7^ cells. The cell cryopreservation solution is a compound electrolyte solution containing 5% human serum albumin and 10% dimethyl sulfoxide (DMSO). |
| **Trial design and protocol** | Following the "3+3" dose escalation design principle, three escalating dose groups A, B, and C were established and 3 subjects were enrolled in each dose group sequentially. Groups A, B, and C received 0.5×10^6^ cells/kg, 1.0×10^6^ cells/kg and 2.0×10^6^ cells/kg respectively, intravenously infused once a week for four weeks (4 times). During the dose-escalation period, the occurrence of adverse reactions in the three groups was observed and dose-limiting toxicity (DLT) was judged. Once dose-limiting toxicity occurs, the investigator will decide to add 3 subjects to the current dose group (i) or the lower dose group (i-1, i≠ the lowest dose group) according to the number of DLT cases to continue observation or stop the trial. According to the safety data of the dose-escalation period, the researchers selected an appropriate dose expansion group (A or B or C) to enroll 6 subjects for the dose-expansion period to further observe the efficacy of UC-MSCs. |
| **operation process of cell product infusion** | Subjects should be given 5mg dexamethasone to prevent post-infusion reactions prior to infusion, and the infusion duration should generally not exceed 1 hour. During infusion, patients' vital signs and adverse reactions should be closely observed. If adverse symptoms occur, infusion speed should be slowed down or stopped as appropriate. |
| **Treatment course** | 28 days |
| **Trial schedule** | - From January 2019 to June 2019, carry out research on project data and complete the launch of the project, including further standardizing the trial process, printing CRFs, clinical diary, informed consent, and other documents, improving the design of the clinical trial protocol, obtaining ethical approval, and preparing for the launch meeting and the work arrangement before clinical trial enrollment; - From June 2019 to June 2021, conduct subject recruitment and clinical study; It is planned to collect 15 enrolled subjects within 24 months; - From June 2021 to December 2021, subjects are followed up, biological samples are tested, and data are collected. - From January 2022 to December 2022: Complete clinical research report and sort out papers. |
| **Follow-up plan and schedule** | Patients will be followed up for 6 months after infusion of umbilical cord-derived mesenchymal stem cells. |

# 1. Title

A clinical trial of umbilical cord-derived mesenchymal stem cells (UC-MSCs) for the treatment of refractory immune thrombocytopenia (ITP)

# 2. Background and Basis

Immune thrombocytopenia (ITP) is an organ-specific autoimmune disease characterized by decreased platelet count and mucocutaneous bleeding due to the increased destruction and impaired production of platelets associated with autoimmunity. Current studies suggest that the immunodeficiency mechanism of ITP is complex and heterogeneous, and the exact pathogenesis is difficult to elucidate. The mechanisms underlying the development of ITP are multi-step processes involving the collaborations of T lymphocytes, B lymphocytes, antigen-presenting cells (APCs), and monocyte-macrophages system. Autoreactive B lymphocytes secrete antiplatelet antibodies, leading to platelet destruction, T lymphocyte activation, and dysplasia of megakaryocytes. In patients with ITP, there is a cytotoxic T cells 1 (Tc1)/ cytotoxic T cells 2 (Tc2) drift and T helper cells 1 (Th1) / T helper cells 2 (Th2) imbalance which caused by Th1 cell hyperpolarization. Regulatory T cells (Tregs) are key cell subsets in maintaining peripheral immune tolerance and can suppress overactivated immune responses. In patients with ITP, not only the proportion of peripheral Tregs is reduced, but also the immunoregulatory function of Tregs is defective. In addition, complement-mediated platelet lysis and cytotoxic T lymphocyte (CTL) -mediated platelet lysis also play important roles in the pathogenesis of ITP.

Mesenchymal stem cells (MSCs) are a group of cells derived from stromal cells, which can be isolated from a variety of tissues, such as bone marrow (BM), adipose tissue, umbilical cord, umbilical cord blood, and synovial tissue. MSCs have various biological properties of highly proliferation in vitro, multilineage differentiation, hematopoiesis supporting, and immune regulation. They are even used as seed cells for tissue engineering and carriers for gene therapy. Research about MSCs has penetrated many medical fields and has become a hot spot in life science research. In addition to the ability of self-renewal and multilineage differentiation, bone marrow-derived mesenchymal stem cells (BM-MSCs) can promote the proliferation and differentiation of hematopoietic stem cells (HSCs) by secreting hematopoietic growth factors or directly contacting with HSCs to maintain the long-term hematopoietic capacity, and it can also exert immunoregulatory effect via different mechanisms to maintain immune homeostasis in the bone marrow environment. Because of the low immunogenicity due to the absence of expressing major histocompatibility complex molecules and co-stimulatory molecules, MSCs can be used for cell therapy without human leukocyte antigen (HLA) matching, and rarely induce allogeneic rejection after infusion. Up to now, MSCs have been widely used in the treatment of autoimmune and inflammatory diseases such as graft versus host disease (GVHD) and systemic lupus erythematosus (SLE). Studies suggest that, MSCs exert immune regulation function mainly through direct cell to cell contact and paracrine behaviors. In vitro experiments have shown that after contacting with T cells, MSCs will secrete a large amount of soluble cytokines (IL-6, TGF-β, IDO) to inhibit the proliferation of T cells, and can also up-regulate the expression of Treg. Besides, MSCs can also regulate the immune balance by interfering with DC maturation or maintaining the proportion of immature DC, inducing Th2 cell differentiation.

Currently, MSCs have been approval for clinical trials in a variety of inflammatory diseases due to their powerful immune regulation function and extremely low immunogenicity. MSCs can effectively reduce the incidence of GVHD after hematopoietic stem cell transplantation, and also have a certain effect on the treatment of aplastic anemia. This provides a theoretical and practical basis for us to use MSCs to improve the immune imbalance in patients with ITP.

Traditional therapies of ITP in adults include first-line treatments (glucocorticoids with or without intravenous immunoglobulin (IVIG)) and second-line treatments (thrombopoietin (TPO), TPO receptor agonists, splenectomy, and immune-suppressive agents (such as Rituximab, Vincristine, and Azathioprine)). As one of the most common hemorrhagic diseases, ITP has a poor response to the current treatment and most patients need long-term medication maintenance treatment to alleviate bleeding symptoms, which seriously affects their quality of life and increases the economic burden on patients. Therefore, for adult ITP patients, especially refractory ITP patients, there is an urgent need for new treatments of solutions to solve this clinical dilemma. At present, some studies at home and abroad have tried to utilize the immunomodulatory function of MSCs to treat ITP patients and achieved certain effects. However, these results are all from small-sample case reports, and lack of credibility. Therefore, we designed this clinical trial to provide a definite clinical basis for the treatment of refractory ITP with UC-MSCs.

# 3. Objective and Endpoints of the Study

## 3.1 Objective of the Study

- Primary objective:

To observe the incidence of adverse events in patients after UC-MSCs infusion, and to preliminarily evaluate the safety of clinical infusion of UC-MSCs.

- Secondary objectives:

1. To preliminarily evaluate the effectiveness of UC-MSCs in the clinical treatment of refractory ITP patients;
2. To preliminarily evaluate the pharmacokinetics characteristic of UC-MSCs in patients with primary ITP;
3. To preliminarily evaluate the immunogenicity of UC-MSCs in patients with primary ITP;
4. To explore the changes in immune function before and after UC-MSC infusion.

## 3.2 Study Endpoints

- Primary endpoint:

Safety endpoint: the safety and tolerance of UC-MSCs in patients with primary ITP. The safety and tolerance of UC-MSCs will be evaluated according to the incidence and severity of adverse events and serious adverse events (according to NCI CTCAE 5.0 standard).

- Secondary endpoints:

Effectiveness endpoints:

1. Platelet counts at each visit point to evaluate the response rate.
2. Percentage of subjects with platelet counts≥50×10^9^/L and ≥100×10^9^/L at least once respectively.
3. Percentage of subjects with platelet counts ≥ 30×10^9^/L and 2-fold increase from baseline at least once.
4. The time required from the first infusion to platelet counts first ≥ 50×10^9^/L.
5. Percentage of subjects receiving emergency treatment
6. Percentage of subjects with reduced concomitant medications.
7. The longest duration of the subject's platelet counts continuously ≥ 30×10^9^/L.
8. Changes in bleeding scores (WHO bleeding scores) throughout treatment.

Pharmacokinetic endpoint:

Pharmacokinetic characteristics of UC-MSCs in patients with primary ITP, especially the concentration changes of UC-MSCs in peripheral blood.

Immunogenicity endpoint:

Incidence of UC-MSCs antibodies.

Other study endpoints:

Changes in immune status in vivo after UC-MSCs infusion.

# 4. Expected Effect

Platelet counts in some subjects show an upward trend and eventually increase significantly after UC-MSC infusion. No obvious adverse events caused by UC-MSC infusion happen, and the vital signs of patients are normal.

# 5. Study Design and Statistical Methods

## 5.1 Study Design

This is a single-centre, open-label, single-arm study, which is divided into two-stage: dose-escalation stage, and dose-expansion stage.

In the dose-escalation stage, three successively increasing dose groups were set up, and the initial dose of the study was the lowest dose group. Subject enrollment, judgment and treatment of dose-limiting toxicity (DLT) refer to the traditional "3+3" dose-escalation design principle. That is, starting from the lowest dose group, 3 subjects were enrolled each time. If no DLT is observed, the trial will be continued at the next level dose; if DLT occurs in one of three patients, three more patients will be enrolled in the current dose, and when no DLT occurs anymore, the trial will be continued at the next level dose. If 2 or more DLTs occur in the 3 or 6 patients, the dose escalation will be stopped, and the current dose will be determined as the maximum tolerated dose (maximum tolerated dose, MTD). The flow of this trial is shown in Figure 1. Considering the safety of UC-MSCs, there will be 9 to 12 patients enrolled in the dose-escalation stage.

[figure not shown]
**Figure 1.** “3 + 3” dose-escalation protocol

[figure not shown]
The final dose in the dose-expansion phase will be determined based on the MTD in the dose-escalation phase, safety, efficacy, and opinion considered by the principal investigator, six patients will be enrolled in the dose-expansion stage to preliminarily explore the efficacy.

**Figure 2.** Six subjects will be enrolled to further evaluate the safety and efficacy of this dose infusion of umbilical cord MSCs

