# Usage, Dosage, Time and Course of Umbilical Cord-derived MSCs

## 9.1 Usage and Dosage of Umbilical Cord-derived MSCs

1. Name of cell products: Umbilical cord-derived MSCs.
2. Specification: 5mL/bag, the main component is MSCs derived from human umbilical cord cultured in vitro, containing 2.0×10^7^ cells. The cell cryopreservation solution is a compound electrolyte solution containing 5% human serum albumin and 10% dimethyl sulfoxide (DMSO).
3. Usage of cell products: Divide into 3 dose-escalation groups (Group A, Group B, and Group C) in turn, with 3 subjects in each group and proceed sequentially from low dose to high dose group according to the principle of dose-escalation. The specific number of subjects in the group is based on a traditional "3+3" dose-escalation protocol, 3 subjects will be enrolled each time, and if no DLT occurs in 3 cases, the trial will be continued at the next level dose; if DLT occurs in 1 of 3 patients, 3 more patients will be enrolled in the current dose, and when no DLT occurs anymore, the trial will be continued at the next level dose. If 2 or more DLTs occur in the 3 or 6 patients, the dose escalation will be stopped, and the current dose will be determined as the MTD.
4. 3 dose-escalation groups- Group A, Group B, and Group C:

- The dose of each infusion in Group A is 0.5×10^6^ cells/kg, intravenous infusion, once a week for a total of 4 times;
- The dose of each infusion in Group B is 1.0×10^6^ cells/kg, intravenous infusion, once a week for a total of 4 times;
- The dose of each infusion in Group C is 2.0×10^6^ cells/kg, intravenous infusion, once a week for a total of 4 times;

According to the above test results, the investigator will determine a specific dose experimental group (one of Group A, B, or C), and expand the sample size of the subjects to 6 cases.

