# Compassionate use Regimen:

1. Applicable subjects: In this study, subjects who have no obvious adverse reactions after umbilical cord-derived MSCs infusion and respond to the treatment, if the platelet count decreases again, and is judged as relapse by the investigator, and the subjects request another infusion, umbilical cord-derived MSC infusion therapy could be given again;
2. Response (R) is defined as platelet counts ≥ 30 × 10^9^/L after MSCs treatment for at least 2 times (7 days apart), and at least doubling of the baseline count with no bleeding.
3. Relapse is defined as subjects who are judged to respond to treatment after the infusion of UC-MSCs by the investigator, and whose platelet count is found to be less than 30 × 10^9^/L again after follow-up or with bleeding.
4. The inclusion and exclusion criteria, management of infusion and concomitant medications, and emergency treatment for compassionate dosing regimen are consistent with this protocol.
5. Dose of re-infusion: the final dose used in the dose-expansion phase.
6. Infusion time: At least 16 weeks after the first infusion of UC-MSCs in this study.
7. Evaluate the efficacy and safety of umbilical cord-derived MSCs again, complete the pharmacokinetic study, detect the production of MSCs’ antibodies, and monitor the immune function;
8. Continued follow-up time: at least 16 weeks after the first dose of UC-MSC infusion in the supplemental regimen.

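### Sections 5.1 and 9.1 label the dose that fails the 3+3 stopping rule as the MTD, and no visible text keeps that dose out of the expansion stage

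*Protocol*

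**What the plan says.** Section 5.1 bases enrolment and the handling of DLTs on the traditional 3+3. Escalation goes on after 0 DLTs in 3 patients, or after 1 in 3 followed by none in 3 more. With 2 or more DLTs among 3 or 6 patients, "the dose escalation will be stopped, and the current dose will be determined as the maximum tolerated dose". Section 9.1 repeats the rule: "the dose escalation will be stopped, and the current dose will be determined as the MTD".

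The expansion dose in section 5.1 is "determined based on the MTD in the dose-escalation phase, safety, efficacy, and opinion considered by the principal investigator". Section 9.1 and the synopsis both allow it to be any of Groups A, B or C; the synopsis ties the choice to the safety data from escalation.

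The synopsis defines no MTD. After a DLT it says the investigator "will decide to add 3 subjects to the current dose group (i) or the lower dose group" (i-1, not available at the lowest dose), or stops the trial, depending on the number of DLTs. The text of sections 5.1 and 9.1 contains no step down.

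The Compassionate use Regimen sets the "Dose of re-infusion: the final dose used in the dose-expansion phase".

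**The concern.** The protocol names a standard design and then gives its key output the wrong meaning. In the traditional 3+3, the dose at which 2 or more patients have a DLT has exceeded the MTD, and the MTD is sought below it. Here the dose called maximum tolerated is always one that failed the protocol's own test for going on.

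Three consequences follow.

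- The MTD is one of the four stated inputs to the expansion dose, and nothing in the visible text bars a dose that met the stopping rule from being expanded.
- The re-infusion dose equals the expansion dose, so a responder from a lower group could be re-infused at the mislabelled dose.
- Safety and tolerance are the primary endpoint (section 3.2), so a misnamed MTD would misstate a central result even if a lower dose were expanded.

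The synopsis, with its option to add patients at i-1, points the other way. Staff working from the synopsis and staff working from section 5.1 or 9.1 could act differently on the same data.

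**Working it through.** **Inputs from the protocol.** Doses are 0.5, 1.0 and 2.0 × 10^6 cells/kg (section 9.1), so each step is 2-fold. The escalation and stopping rules are in section 5.1. The expansion stage has 6 patients, and the stated escalation total is 9–12 (section 5.21). The minimum total reproduces: 3 groups × 3 + 6 = 15 (section 7).

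**Step 1: what the label means.** A dose passes with 0/3 or 1/6. A dose labelled MTD has at least 2/6 = 33% observed DLTs, and up to 3/3 = 100%. If the rule fires at C, the conventional MTD is sought at B or below, and if at B, at A. If it fires at A, there is none. If it never fires, the text defines no MTD.

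**Step 2: chance that a dose gets the label.** With true DLT rate p at a dose:

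P(stop at that dose) = S(p) = 1 − (1−p)³ − 3p(1−p)⁵

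This gives S = 0.09, 0.29, 0.51, 0.69 and 0.83 at p = 10, 20, 30, 40 and 50%. The more toxic the dose, the more likely it is to be called tolerated.

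**Step 3: the three-level ladder.** The protocol gives no DLT rates, so the A/B/C rates below are assumptions running from low to high toxicity.

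P(stop at A) = S(A); P(stop at B) = [1−S(A)]·S(B); P(stop at C) = [1−S(A)]·[1−S(B)]·S(C)

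Worked for 2/5/10%: S = 0.00457, 0.02656, 0.09385.

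- Stop at A: 0.00457
- Stop at B: 0.99543 × 0.02656 = 0.02644
- Stop at C: 0.99543 × 0.97344 × 0.09385 = 0.09094
- Total: 0.122

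**Step 4: excess DLTs if the stopped dose is expanded instead of the level below.** For the same rates, P(stop above A) = 0.02644 + 0.09094 = 0.1174.

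- Mean true rate at the labelled dose: (0.02644 × 0.05 + 0.09094 × 0.10) / 0.1174 = 0.0887
- Mean true rate one level below: (0.02644 × 0.02 + 0.09094 × 0.05) / 0.1174 = 0.0432
- Excess in 6 patients, given a stop above A: 6 × (0.0887 − 0.0432) = 0.273
- Not conditioned on a stop: 0.273 × 0.1174 = 0.032

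| Assumed A/B/C DLT rate | P(any stop) | P(stop above A) | Mean rate, labelled / one below | Excess DLTs per 6, given stop above A | Excess, unconditional |
|---|---|---|---|---|---|
| 0.5/1/2% | 0.006 | 0.0057 | 0.0180 / 0.0090 | 0.05 | 0.0003 |
| 1/2/5% | 0.032 | 0.0310 | 0.0456 / 0.0185 | 0.16 | 0.005 |
| 2/5/10% | 0.122 | 0.1174 | 0.0887 / 0.0432 | 0.27 | 0.032 |
| 5/5/5% | 0.078 | 0.0510 | 0.0500 / 0.0500 | 0 | 0 |
| 5/15/30% | 0.609 | 0.5819 | 0.2533 / 0.1188 | 0.81 | 0.47 |
| 5/15/40% | 0.755 | 0.7284 | 0.3378 / 0.1251 | 1.28 | 0.93 |

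The last two columns assume that the stopped dose is the one expanded, so they are upper limits on the effect and not forecasts.

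**The case against.** The strongest reply is that the wrong label would seldom matter.

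- **DLTs should be rare.** Section 4 expects no obvious adverse events. The DLT definition is strict: new, grade 3 or higher, related to the infusion, and not down to grade 1 within 72 hours despite treatment. Nothing in the protocol supports the two high-toxicity rows; in the others the unconditional excess is at most 0.03 DLTs per 6 patients.
- **Nothing requires expansion at the MTD.** Section 5.1 also lists safety, efficacy and investigator opinion, and the synopsis refers to safety data. Section 13.4 calls for suspension after a serious safety problem.
- **The synopsis already has the i-1 step**, and Figures 1 and 2, not available here, may show it or an exclusion.
- **Re-infusion is a remote route.** It is limited to "subjects who have no obvious adverse reactions after umbilical cord-derived MSCs infusion and respond to the treatment", and they must then relapse and ask for it.
- **Timing.** Recruitment was scheduled to end in June 2021, the month of version 3.0, so for this version the label may matter mainly for re-infusion and reporting.

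Most of this stands as a limit on size. It does not correct the rule. The safeguards are discretionary and set no dose cap. A figure would not amend the sentence that appears in two sections. A stopping rule exists for the unlikely bad outcome, which is where this one gives the wrong answer.

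**Conclusion.** The concern holds. The MTD clause in sections 5.1 and 9.1 is wrong for the design the protocol names and conflicts with the protocol's own criterion for going on. When it operates, the label is one level (2-fold) too high, or names a failed dose at Group A.

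The practical size depends on unknown DLT rates. It is negligible if toxicity is as low as the sponsor expects and approaches one extra DLT per 6 expansion patients at 5/15/40%, assuming the stopped dose is expanded. That no text excludes the stopped dose is a statement about the visible text only, since the figures could not be read. This should be fixed: it is a clear error in a safety rule, stated twice, and cheap to correct.

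**What to change.** In sections 5.1 and 9.1, replace the MTD clause with wording to this effect:

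- A dose with 2 or more DLTs in 3 or 6 patients exceeds the MTD.
- The MTD is the highest lower dose with at most 1 DLT in 6 patients; if only 3 were treated there, 3 more are added.
- If Group A meets the stopping rule, at first or after a step down, no MTD is declared and there is no expansion.
- If no dose meets the rule, the MTD is not reached and Group C is the highest permitted dose.

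Add one sentence: the expansion dose, and so the re-infusion dose, may not exceed the MTD, or Group C if the MTD is not reached. The choice among permitted doses stays with the clinical team. The condition that only 3 were treated is an addition; the synopsis gives the i-1 step without it.

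The cost is mainly wording. The step down usually adds 3 patients after a stop, or 6 if it repeats. The 9–12 escalation range should be restated, although the rule as written can already exceed 12. The maximum is 18 (3 levels × 6) either way.

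| Assumed A/B/C DLT rate | P(more than 12), as written | P(more than 12), with step down |
|---|---|---|
| 1/2/5% | 1% | 3% |
| 2/5/10% | 4% | 10% |
| 5/15/30% | 13% | 31% |
| 5/15/40% | 13% | 34% |
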